### General study methodology

This is a French bicentre (Clinique Bretéché and CHU/University Hospital Nantes), randomized, comparative, double-blind, sham-controlled trial conducted in two parallel arms: tDCS (35 patients) and sham tDCS (35 patients).

Centralized randomization will be performed by software and will be specific to each of the 2 centres. Patients will not be informed about whether they have been allocated to the active tDCS arm or the sham tDCS arm. Physicians performing the tDCS technique and the evaluating physicians will also be blinded to the type of treatment delivered (see “Interventions: tDCS and follow-up intervention”).

Doses of analgesic medications (opioids, antiepileptics and antidepressants) must be stable for at least 48 hours (D-3, D0) prior to inclusion in the study. The level of analgesic treatment will be assessed by MQS. Analgesic doses may be able to be decreased from the first day of tDCS depending on its analgesic effect. One of the objectives of tDCS is to decrease the doses of analgesics in order to avoid a state of drowsiness or torpor associated with impaired quality of life.

#### Inclusion criteria

Patients between the ages of 18 to 80 years with cancer pain refractory to medical treatment (mean NRS ≥ 4/10 on 2 consecutive days) in the palliative care setting.Patients agreeing to participate in a research protocol in this palliative care setting.

#### Exclusion criteria

Patients younger than 18 years or older than 80 years.NRS < 4/10 (pain controlled by adapted medical treatment and global management).Patients unable to fill in the various questionnaires, specifically chosen to be simple and easy to fill in.Patients refusing to sign the informed consent form.Patients with cognitive impairment, metal implantation in the brain and mood disordersPatients with a life expectancy less than 3 weeks (duration of study follow-up).

### Recruitment modalities

Patients will be recruited from the Center 1 (Clinique Bretéché rehabilitation and palliative care unit, Nantes), and Center 2 (CHU/University Hospital Nantes palliative care unit). The inclusion of one patient per month corresponds to the recruitment, treatment and follow-up capacities of each of these centres in accordance with the protocol. The study will last 24 months.

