**Fig. 1 Fig1:**
[figure not shown]
Study plan: the study will last 24 days (D-3 to D21) including a 3-day inclusion period (D-3-D0), a 5-day treatment period (D0-D4) and a 16-day follow-up period after stopping treatment (D8, D14, D21). Treatment consists of a daily tDCS session on 5 consecutive days. Patients will be randomized to 2 arms (1:1 ratio): active tDCS and sham tDCS. Patients and investigators will be blinded to the results of randomization (double-blind). The primary objective will be a significant reduction of pain evaluated by a numerical rating scale (NRS) from 0 to 10 between the baseline score recorded between D-3 and D0 and the score recorded 4 days after stopping treatment (D8)

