### Statistical analysis

Statistical justification of the sample size: a 2-point improvement of the numerical rating scale is considered to be clinically relevant [51], which is supported by data from the study conducted by Cheung [55] on the efficacy of ketamine in a population of patients in palliative care setting (see “Clinical Parameters”).

As this is the first protocol dedicated to the treatment of painful patients in a palliative care setting with tDCS, we did not find any evidence in the literature that could help us justify the number of needed patients for the evaluation of the other clinical parameters, apart from the NRS.

On the basis of these hypotheses:A mean NRS difference of 2 points between the active tDCS arm and the sham tDCS arm,Standard deviation of 2.8,Power of 80%.Alpha risk of 5%,

32 patients per arm would be necessary, i.e. a total of 64 patients. In order to ensure sufficient power, an additional 10% of patients will be included in the study, i.e. a total of 70 patients.

The study will therefore include 70 patients: 35 in the tDCS arm and 35 in the sham tDCS arm.

The variables measured on inclusion will be described for all patients and in each of the two arms by number and percentage for each modality for qualitative variables and by minimum, maximum, mean, standard deviation and quartiles for quantitative variables. The primary efficacy population will be a modified intention-to treat (mITT) population, comprising all randomized patients who have received at least one tDCS session (active or sham) and who were evaluated on D0 (baseline) and on D8.

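### The stated recruitment rate and 24-month duration allow at most 48 patients, which cannot be squared with the planned 70 or the 64 needed for 80% power

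*Protocol article*

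**What the plan says.** In the protocol article, Recruitment modalities names two recruiting units and sets the pace: "The inclusion of one patient per month corresponds to the recruitment, treatment and follow-up capacities of each of these centres". The next sentence reads: "The study will last 24 months". General study methodology confirms the number of centres: "This is a French bicentre (Clinique Bretéché and CHU/University Hospital Nantes), randomized, comparative, double-blind, sham-controlled trial".

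The target is set in Statistical analysis. The inputs are "A mean NRS difference of 2 points between the active tDCS arm and the sham tDCS arm", "Standard deviation of 2.8", 80% power and a 5% alpha risk, and the result is "32 patients per arm would be necessary, i.e. a total of 64 patients". A 10% addition follows: "The study will therefore include 70 patients: 35 in the tDCS arm and 35 in the sham tDCS arm". The Abstract and General study methodology repeat the 35 per arm.

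The legend of Fig. 1 gives each patient's course as 24 days, from D-3 to D21. The primary efficacy population (Statistical analysis) is limited to randomized patients who had at least one session and were assessed on both D0 and D8.

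**The concern.** The rate is described as a capacity that covers recruiting, treating and following patients, so it does not read as a cautious minimum that the centres expect to exceed. Multiplied out over two centres and the stated duration, it falls well below both the 70 to be enrolled and the 64 on which the power rests. The article mentions no further centre, faster phase, extension, or rule for stopping short of 70.

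One of two things must then give. Either the trial runs well past its stated end, or it closes on time with too few patients for its stated power. Both can be foreseen now. A decision to extend or stop early is easier to defend when planned in advance than when taken mid-trial.

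**Working it through.** **Inputs** (all from the protocol article)
- Rate: 1 patient per month per centre (Recruitment modalities)
- Centres: 2 (General study methodology; Recruitment modalities)
- Duration: 24 months (Recruitment modalities)
- Course per patient: 24 days (Fig. 1 legend)
- Needed: 32 per arm, 64 in total; enrolled: 70 (Statistical analysis)
- Difference 2, SD 2.8, power 80%, alpha 5% (Statistical analysis)
- Assumption: alpha is two-sided. The article does not say, but only this choice gives its figure.

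**1. Reproduce the plan's own figure.** The test is a two-sample t-test with n per arm, 2n − 2 degrees of freedom and noncentrality 2 / (2.8 × √(2/n)).
- n = 31: power 79.0%
- n = 32: noncentrality 2 / (2.8 × 0.25) = 2.857; power 80.3%

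The smallest n that reaches 80% is 32, as stated. The normal approximation gives 31 per arm, and a one-sided 5% test by the same approximation gives 25. For the 10% addition, 64 × 1.10 = 70.4, stated as 70. The calculation is sound.

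**2. Accrual within the stated duration.** 2 centres × 1 per month × 24 months = 48.
- Against 70: short by 22 (22/70 = 31%)
- Against 64: short by 16 (16/64 = 25%)

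The 48 is slightly generous. It uses all 24 months for accrual, although the last patient's course must also fit if 24 months is the total duration.

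**3. Time needed at the stated rate.** 70 / 2 = 35 months of accrual, plus about one month for the last patient's follow-up, so about 36 months, or 12 more than stated. Enrolling 64 alone would take 64 / 2 = 32 months.

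**4. Rate needed in the stated time.** 70 / (2 × 24) = 1.46, so about 1.5 per centre per month (1.5 × 2 × 24 = 72).

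**5. Power by number of patients** (same t-test)

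| Situation | Per arm | Power |
|---|---|---|
| All 70 evaluable | 35 | 83.8% |
| 64 evaluable | 32 | 80.3% |
| Stop at 24 months, all 48 evaluable | 24 | 67.8% |
| Stop at 24 months, plan's own ratio: 48 × 64/70 = 43.9, about 44 | 22 | 63.9% |
| Stop at 24 months, 10% lost: 48 × 0.90 = 43.2, about 43 | 21.5 | 62.8% |

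The last two rows treat the 10% addition as an allowance for patients without a usable D8 assessment. The article says only that it is there to secure power, so this is an assumption.

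**6. Other readings.** Treating the 24 months as accrual only still gives 48. Treating the rate as one per month for both centres together would give 24, but the text attaches the capacity to each centre. Neither reading reaches 64 or 70.

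**The case against.** The strongest reply is that the 24 months is a forecast in a paragraph on recruitment, not a closing rule. Enrolment is fixed at 70 in three places, and nothing says that recruitment ends at month 24 whatever the number reached. If the trial recruits to 70, the power is as stated and the only error is a calendar that is too short. This stands. A reader might infer from the 48 that the trial has about 68% power instead of 80%, or that the sample-size calculation has failed. The document supports neither: the 80% belongs to 64 patients and reproduces, and the lower figure applies only if enrolment stops at 24 months.

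It also stands that the article does not show which figure is wrong. A reader might take the duration to be the error, but a misstated rate or an omitted centre would explain the gap equally well.

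Finally, the mismatch changes no endpoint, randomization, blinding or analysis model, and its likeliest result is delay. That is fair as to its weight, but it does not remove the contradiction. All three figures stand in the same article, so condensing a fuller protocol does not explain the conflict between them.

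**Conclusion.** The point holds as an internal inconsistency. At the stated capacity and duration at most 48 patients can be enrolled, 31% below the planned 70 and 25% below the 64 required. The consequence depends on which figure gives way. If 70 is kept at the stated rate, power is unaffected and the duration is understated by about 12 months. If the calendar is kept at the stated rate, power for the 2-point difference is at most about 68%, and about 63–64% with roughly 10% not evaluable on D8. The power figures assume a two-sided 5% t-test with SD 2.8 and equal arms. The 68% is an upper bound because it counts every enrolled patient as assessed on D8.

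**What to change.** Reconcile the rate, the number of centres, the duration and the sample size, and correct whichever is wrong:

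- **Rate right, 70 kept:** restate the duration in Recruitment modalities as about 36 months (35 of accrual plus the last patient's follow-up).
- **Rate or number of centres wrong:** restate it. With two centres, about 1.5 patients per centre per month would be needed to enrol 70 in 24 months.
- **Rate, centres and 24 months all fixed:** restate the achievable size (about 48) and its power (at most about 68%) in the Abstract, General study methodology and Statistical analysis.

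The edit itself is a few figures. The price is a longer stated calendar in the first case or a less favourable stated power in the third. No patients beyond the planned 70 are needed.

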### Study plan (Fig. 1)

#### Screening visit (D-3)

Verification of inclusion and exclusion criteria. Patients will be provided with the information sheet and will be asked to sign the informed consent form. The patient will be provided with NRS forms (3 assessments per day for 48 hours). For organizational reasons, this screening visit will be held on a Friday. NRS scores will be recorded on Saturday and Sunday so that inclusion or exclusion of the patient can be decided on Monday.

**Fig. 1 Fig1:**
[figure not shown]
Study plan: the study will last 24 days (D-3 to D21) including a 3-day inclusion period (D-3-D0), a 5-day treatment period (D0-D4) and a 16-day follow-up period after stopping treatment (D8, D14, D21). Treatment consists of a daily tDCS session on 5 consecutive days. Patients will be randomized to 2 arms (1:1 ratio): active tDCS and sham tDCS. Patients and investigators will be blinded to the results of randomization (double-blind). The primary objective will be a significant reduction of pain evaluated by a numerical rating scale (NRS) from 0 to 10 between the baseline score recorded between D-3 and D0 and the score recorded 4 days after stopping treatment (D8)

#### Inclusion visit (visit 1) (D0)

Recording of NRS scores for 48 hours (D-3 to D-1) allowing inclusion of the patient. Recording of clinical parameters such as age, sex, weight, height, etc., medical history, previous and concomitant treatments, vital signs. Baseline assessment: NRS, BPI, ESAS, HADS, STAI-Y and MQS (see secondary endpoints). Randomization (by centre, 1:1 ratio). Study personnel (physician and nurses specialized in pain management) will be blinded to the results of randomization.

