#### Analysis of the primary endpoint

Analysis of the primary endpoint, the pain NRS, will be performed on the mITT population.

The mean NRS score on D8 will be compared between the active tDCS arm and the sham tDCS arm using a mixed linear model in order to take stratification factors into account.

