### Randomization

Centralized randomization will be performed on D0 after verification of the inclusion criteria. Randomization will be performed under double-blind conditions and will be stratified according to the mean baseline pain intensity (4–6 or 7) over the last 48 hours before inclusion and according to centre.

Patients will be randomized to receive either active tDCS or sham tDCS for the 5 treatment days defined by the protocol. The randomization ratio will be 1:1. Randomization will be stratified by centre by means of the Ennov Clinical electronic CRF (https://fr.ennov.com/getions-essais-cliniques/) by logging onto the website: https://nantes-lrsy.hugo-online.fr/CSOnline/ after obtaining the patient’s informed consent on D0. The inclusion number and randomization arm will be automatically allocated at the time of randomization. A confirmation e-mail will be sent to the person who performed randomization and to all other people concerned.

Randomization lists will be established by a Nantes university hospital research promotion department statistician.

A patient registered in the trial, to whom treatment has been allocated and documented, will be considered to be randomized. A patient cannot be included, evaluated or randomized in the trial more than once.

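### The protocol names the randomisation strata inconsistently (centre plus baseline pain class, or centre), so baseline pain may be missing from the primary model

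*Protocol article*

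**What the plan says.** Four places in the protocol article describe how allocation is stratified.

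- Randomization, first paragraph: allocation is "stratified according to the mean baseline pain intensity (4–6 or 7) over the last 48 hours before inclusion and according to centre".
- Randomization, second paragraph, which names the system that performs the allocation: "Randomization will be stratified by centre by means of the Ennov Clinical electronic CRF".
- Inclusion visit (D0): "Randomization (by centre, 1:1 ratio".
- General study methodology: "Centralized randomization will be performed by software and will be specific to each of the 2 centres".

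The primary analysis section sets the D8 NRS of one group against that of the other, and describes the method as "using a mixed linear model in order to take stratification factors into account". It lists no factors and names no separate baseline NRS covariate. Several models under Analysis of secondary endpoints refer to stratification factors in the same way. The Study objective section defines the primary endpoint differently, as the change in NRS from D0 to D8.

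**The concern.** One statement implies four strata (two centres by two pain classes). The others, read literally, imply two. This matters beyond the list itself, because the covariates of the primary model are defined only by reference to the strata. As the analysis section is written, stratification is the only way baseline pain can enter a comparison of D8 scores. If the electronic CRF was set up from the centre-only sentence, baseline pain is neither balanced by design nor adjusted for, although it is likely to predict D8 pain. A statistician working from this text could defend either covariate set.

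**Working it through.** **Comparison of the statements.** Pain class and centre: one place (Randomization, first paragraph). Centre with no mention of pain: three places (Randomization, second paragraph; D0 visit; General study methodology). The last of these says that randomisation is specific to each centre and does not use the word stratified. None of the three says that centre is the sole factor. The sharpest conflict is between the two consecutive paragraphs of the Randomization section.

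**The plan's sample size.** Inputs from Statistical analysis: difference 2, SD 2.8, power 80%, alpha 5% (taken as two-sided). A two-sample t-test needs 31.76, so 32 per arm, with power 80.3%. Then 64 × 1.10 = 70.4, about 70. The plan's figures reproduce. They use no baseline adjustment, so an analysis without baseline pain still meets the planned 80%.

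**Chance imbalance if pain is not a stratum.** The protocol does not give the high-pain share p, so 30–50% is assumed. With 35 per arm, a gap of 15 points means at least 6 patients (0.15 × 35 = 5.25). Take two independent binomial(35, p) counts, X and Y:

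- p = 0.3: P(|X − Y| ≥ 6) = 15%
- p = 0.4: 18%
- p = 0.5: 19%

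Fixing the total number of high-pain patients among the 70 (hypergeometric) gives 12%, 22% and 15% for the same shares. These values are uneven because the counts are discrete. At 32 per arm the binomial figure is 22–26%, but 35 per arm are randomised.

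**Gain from adjustment, 32 evaluable per arm.** The protocol gives no baseline-to-D8 correlation r, so 0.3–0.6 is assumed, and 2.8 is taken as the SD of the D8 score.

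Continuous baseline NRS: residual SD = 2.8 × √(1 − r²).

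| r | residual SD | power |
|---|---|---|
| 0 | 2.800 | 80.3% |
| 0.3 | 2.671 | 83.9% |
| 0.4 | 2.566 | 86.6% |
| 0.5 | 2.425 | 90.1% |
| 0.6 | 2.240 | 94.0% |

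Simulation, which also pays for the extra model terms and for chance imbalance, gives about 83–94%.

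Pain class: splitting a normal baseline so that 40% are in the high class multiplies r by φ(0.253)/√(0.4 × 0.6) = 0.386/0.490 = 0.788. At r = 0.3 the correlation becomes 0.237, the residual SD 2.720 and the power 82.5%. At r = 0.6 they become 0.473, 2.467 and 89.1%.

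**Separating lists from model.** Simulated power with 64 patients, blocks of 4 and r from 0.3 to 0.6:

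- Centre in both lists and model: about 80%
- Centre-only lists, pain class added to the model: 82–88%
- Four-stratum lists, pain class in the model: 83–89%

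Nearly all the gain comes from the covariate. For a given model, the choice of lists is worth about 2 points or less.

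**The case against.** The strongest reply is that the three places omit pain and do not exclude it. An overview and a visit checklist that mention centre are compatible with a two-factor scheme. The electronic CRF sentence can be read as describing the mechanism. The section devoted to randomisation opens with the full rule, and the analysis section speaks of factors in the plural, where centre would be a single factor. All of this stands, and it makes the two-factor reading the more likely one. It does not settle the matter, because the sentence naming the allocation system gives centre with no other factor.

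It can also be said that covariate lists belong in the SAP, and that the change-from-D0 endpoint brings baseline in through the outcome. An article may leave covariate names to the SAP. Here, though, the article defines the covariates by the strata and then states the strata inconsistently. The change-score definition appears under Study objective, while the analysis section compares D8 scores, so it does not resolve the question.

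The size of the gain is also open to challenge. Entry requires a mean NRS of at least 4, which truncates baseline and tends to lower r; at r of 0.2–0.3 the gain from pain class is only about 0–2 points. That is fair, and it is why the gain is given as a range under an assumption.

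**Conclusion.** The inconsistency is real and its consequence is modest. The text leans towards two factors without fixing them. On the centre-only reading, the D8 comparison has no baseline-pain adjustment. The cost is then some precision and a 15–19% chance of a 15-point or larger gap in high-pain share (35 per arm, 30–50% high pain assumed). With r assumed at 0.3–0.6, the power forgone is the difference between about 80% and 82–88% with pain class, or 83–94% with continuous baseline NRS.

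Three stronger readings are not supported. A reader might infer bias, but any imbalance under 1:1 randomisation is chance. A reader might infer an underpowered trial, but the planned 80% assumes no adjustment. A reader might infer a distorted type I error from stratifying on pain and then leaving it out of the model. The protocol does not describe that combination, since its model takes the stratification factors into account, and the distortion would in any case be conservative.

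**What to change.** 1. Check the randomisation set-up in the electronic CRF. Make General study methodology, the D0 visit and both paragraphs of Randomization state the lists that were actually built: centre and pain class, or centre.
2. In Analysis of the primary endpoint and Analysis of secondary endpoints, name centre and baseline pain as covariates in the NRS models, whichever lists were used. Pain class would do, but the continuous 48-hour mean NRS is preferable because it recovers more precision.
3. If the lists were built by centre only, say so. Adjustment in the model recovers nearly all of what stratification on pain would have given.

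The cost is protocol wording and one check of the system. The sample size does not change, and no new data are needed because the 48-hour NRS is already recorded for eligibility.

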#### Treatment with active or sham tDCS (D0-D4)

Study personnel (physician or trained nurse), but not the patient, will be informed about the results of randomization. tDCS will be delivered daily for 5 consecutive days. The NRS will be scored 3 times a day on these 5 days from Monday to Friday.

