tDCS appears to be more suitable than rTMS for the treatment of palliative care patients, who are often difficult to mobilize, as tDCS can be delivered at the patient’s bedside and possibly even at home, which is not the case with rTMS. tDCS also appears to be rapidly effective (after 5 sessions) in the context of cancer pain, and this effect lasts longer than that of rTMS.

The proposed treatment of refractory cancer pain by tDCS in palliative care patients is a new treatment modality that is well adapted to hospitalised patients. Each patient will receive 20 minutes of transcranial direct-current stimulation daily for 5 consecutive days. One arm will receive active stimulation and the control arm will receive sham stimulation. Patients and investigators will be blinded to the type of tDCS. By improving the patient’s activities of daily living, this treatment will enable the patient to return home under good conditions for both the patient and the caregivers. This treatment can also be continued at home. This strategy is consistent with current guidelines in this field, in which the priorities are improvement of quality of life [20–22], return home [23–25] and decreased workload for caregivers [26].

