### Interventions: tDCS and follow-up intervention

tDCS was tested in healthy subjects from 2000 until 2005, at the time of the first clinical applications in the treatment of chronic pain. tDCS consists of delivering a low-intensity (1 to 2 mA) direct electrical current by means of a pair of electrodes (anode and cathode) applied to the scalp. Electrodes generally have a diameter (round electrode) or a diagonal (rectangular electrodes) ranging from 2 to 3.5 cm. To stimulate a given cortical zone, the anode is placed over of the selected zone, generally identified by means of an EEG headset (10/20 System Positioning). For the treatment of pain, the anode is placed over the primary motor cortex (M1) on the contralateral side to the pain or on the left side in patients with diffuse pain. The cathode is placed over a supposedly neutral cortical zone, usually the contralateral supraorbital cortex with respect to the anode. In this study, the stimulation intensity will be 2 mA using round sponge electrodes 3.5 cm in diameter. As in the case of rTMS, stimulation of M1 is thought to be active by means of the connections between the motor cortex and numerous structures situated away from M1 involved in pain modulation [27]: especially the cingulate cortex, thalamus and rostral ventromedial medulla [28, 29].

A tDCS session generally lasts 20 minutes. The patient may experience a feeling of heat or paraesthesia at the site of the electrodes for the first 30 seconds, but subsequently does not experience any sensations, which is why active stimulation will be delivered for the first 30 seconds of the sham procedure [30, 31]. In this study, patients will receive one daily session for 5 consecutive days. The HDC Kit (Newronika, Milano, Italy) will be used. The system includes a programming module, which allows to choose an active or placebo stimulation mode, which is independent of the stimulation module where there is no indication on the stimulation mode. In this protocol, a nurse programs the device according to the results of the randomization, then is no longer involved in the protocol. The physician who performs the stimulation, using the previously programmed stimulation module, the patient and the evaluating physicians are not aware of the programming mode, and are thus blind.

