More generally, this protocol raises the issue of clinical research in palliative care patients [11], which has been the subject of several studies [33–35], showing that palliative care patients potentially at the end of life were generally in favour of scientific studies designed to improve the quality of life of future patients, even in the absence of a direct personal benefit.

In order not to penalize patients in the placebo group, it is planned to lift the blind at D21 and to offer these patients the active treatment outside the protocol. Patients who have been actively treated and whose pain has recurred after D21 will be offered a second treatment outside the protocol.

As tDCS is a noninvasive technique with few expected adverse effects, the benefit/risk balance is expected to be highly positive for the patient in this context of refractory cancer pain in the palliative care setting.

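### The D0-D4 treatment section informs the physician or nurse of the allocated arm, contradicting every other section that says who is blinded

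*Protocol article*

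**What the plan says.** The section on treatment with active or sham tDCS (D0-D4) states: "Study personnel (physician or trained nurse), but not the patient, will be informed about the results of randomization". Only the patient is left blind.

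The rest of the article describes something else:

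- Background: "Patients and investigators will be blinded to the type of tDCS". The Fig. 1 legend says the same of the randomization result and labels the trial double-blind.
- General study methodology: "Physicians performing the tDCS technique and the evaluating physicians will also be blinded to the type of treatment delivered".
- Inclusion visit (D0): "Study personnel (physician and nurses specialized in pain management) will be blinded to the results of randomization".
- Interventions: a nurse sets the device to active or sham and then leaves the trial. The stimulation module shows no mode. The physician who stimulates does not know it, and "the patient and the evaluating physicians are not aware of the programming mode, and are thus blind".

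Three other statements bear on the point. The section on visits 3 and 4 (D14 and D21) gives assessment to a blinded team. The Randomization section says randomization is done under double-blind conditions, and also: "A confirmation e-mail will be sent to the person who performed randomization and to all other people concerned". Benefits and risks says of the sham group that "it is planned to lift the blind at D21 and to offer these patients the active treatment outside the protocol".

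**The concern.** Who knows the arm is a matter of trial conduct, and no analysis plan can settle it afterwards. A site that worked from the treatment section would tell the staff giving the sessions which arm the patient is in, while the report would describe a double-blind trial.

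This trial is sensitive to that. The NRS is given orally by the patient. It is collected three times a day on the treatment days, and the scores before and after each session are a secondary endpoint. General study methodology allows analgesics to be lowered from the first tDCS day depending on effect. That can move D8 pain and is itself measured by the MQS. The same staff also handle poor tolerance, including whether sessions continue. The primary population requires a D8 evaluation, so knowledge of the arm could also affect who is analysed.

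**Working it through.** **Step 1: set the statements side by side.**

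| Section | Stimulating physician | Study or pain nurses | Evaluators | Patient |
|---|---|---|---|---|
| Background; Fig. 1 legend | blind (as investigator) | not named | blind (as investigator) | blind |
| Interventions | blind | one programming nurse knows, then leaves | blind | blind |
| General study methodology | blind | not named | blind | blind |
| Inclusion visit (D0) | blind (physician) | blind | not named | not named |
| Treatment (D0-D4) | informed (physician or trained nurse) | informed (physician or trained nurse) | not named | blind |
| Visits 3 and 4 (D14, D21) | not named | not named | blind | not named |

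The treatment section is the only outlier. D0 falls under both the inclusion visit and the treatment period, so on that day two headings give opposite instructions for almost the same staff.

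**Step 2: can the sentence mean the programming nurse only?** No. It names a physician, whereas the Interventions section gives programming to a nurse. It also does not confine the knowledge to someone who then leaves the trial.

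**Step 3: does blinded assessment elsewhere cure it?** Only in part. The blinded team is stated under D14 and D21, and the D8 section does not repeat it. General study methodology does blind evaluating physicians without limiting this to a visit, so a blinded D8 rater is a fair reading. Even so, a blinded rater at D8 does not undo what informed staff say, score or change in medication during D0-D4.

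**Step 4: size.** The document gives no bias figure. What can be shown is how sensitive the planned test is.

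- Inputs from the sample-size paragraph: difference 2 points, SD 2.8, power 80%, alpha 5%.
- The plan's own figure: 2 × (1.960 + 0.842)² × 2.8² / 2² = 30.8, so 31 per arm by normal approximation. The two-sample t-test gives 31.76, so 32 per arm, as stated. Then 64 × 1.10 = 70.4, the stated 70. The one-sided formula gives 25, so the plan is two-sided.
- Assumption: no true effect, and a staff-driven between-arm difference of b points at D8.
- Standard error with 35 per arm: 2.8 × √(2/35) = 0.669. With 32 per arm: 2.8 × √(2/32) = 0.700.
- Rejection probability = 1 − Φ(1.96 − b/SE) + Φ(−1.96 − b/SE).

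| Assumed b (points) | 35 per arm | 32 per arm |
|---|---|---|
| 0 | 5.0% | 5.0% |
| 0.25 | 6.6% | 6.5% |
| 0.5 | 11.6% | 11.0% |
| 0.75 | 20.2% | 18.8% |
| 1.0 | 32.1% | 29.8% |

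These rates depend wholly on b, for which there is no source. They are not evidence that such a bias will occur.

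**The case against.** The best defence is that this is one stray sentence. The Interventions section sets out a workable double-blind mechanism, the Discussion says the device was chosen for it, and the D14 and D21 assessors are blinded. Sites work from the full protocol, which is not shown. This stands as far as intent goes: the document does not show that a single-blind design was chosen. It does not remove the contradiction, because the sentence is current text and assigns knowledge of the arm to named roles.

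A reader might go further and infer that the confirmation e-mail spreads the allocation to staff. The document does not support that. The Randomization section does not say that the e-mail shows the arm, and the other people concerned could be the programming nurse. The undefined recipient list is worth clarifying, no more.

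A reader might also infer that unblinding at D21 damages the primary result or makes later allocations predictable. That is not supported either. D21 is 13 days after the same patient's D8 endpoint (21 − 8). Predicting later allocations would need a known block scheme within strata of centre and baseline pain, and an article commonly leaves that scheme to the full protocol. Nor is it secure that each allocation is known before the next inclusion. One patient per centre per month yields 2 × 24 = 48, not 70. If the centres share recruitment equally, reaching 35 each in 24 months means one about every 21 days (730/35 = 20.9), which is roughly the D21 interval itself. What remains is that the order of the D21 assessments and the unblinding is not stated.

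**Conclusion.** The contradiction is real and must be corrected. The treatment section makes D0-D4 single-blind if followed, against five statements that staff are blinded. The finding rests on the text alone and needs no assumption.

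Its effect on the results cannot be sized from the document. The error rates in the working are conditional on an assumed shift and serve only to show that a modest bias would matter at this sample size. The sample size itself reproduces and is not affected.

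The document does not establish that the trial is being run single-blind, that the e-mail discloses the arm, or that the D21 unblinding compromises the D8 comparison.

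**What to change.** Rewrite the sentence in the treatment section so that only the programming nurse described under Interventions is told the randomization result. State that the physician giving tDCS, the other nurses, the evaluators and the patient are not told.

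Two clarifications follow from this:

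- In the Randomization section, confirm that any e-mail showing the arm goes to that nurse alone.
- In Benefits and risks, state that each patient's D21 assessments are recorded before the blind is lifted.

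The cost is a few sentences and, if needed, one notification setting in the electronic CRF. No new role is required, since the programming nurse already exists, and the sample size and analysis do not change.
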